#### **5.3.27. Phenoconversion Visit (Prodromal and Unaffected Genetic Cohort subjects only)**

If a Prodromal or Unaffected Genetic cohort subject is diagnosed with PD or other neurodegenerative disorder in the course of clinical care, then a phenoconversion visit should be completed. The clinical diagnosis of PD or a neurodegenerative disorder can be made by the site investigator if the investigator is also providing clinical care to the participant or by a non-study physician with appropriate training (e.g. non-study neurologist, primary care provider). The

schedule of activities for a phenoconversion visit is below. The phenoconversion visit should occur within 45 days of the site being aware of clinical phenoconversion.

Following the phenoconversion visit, please resume the schedule of activities, starting with the subject's next regularly scheduled visit. However, if the phenoconversion visit occurs within the 2 months prior to an expected annual visit, then the phenoconversion visit will supersede the annual visit and the annual visit will not be conducted.

All assessments and activities listed below should be completed as part of a phenoconversion visit:

- Review of clinical diagnosis\*
- Review of continuing ability to consent/Advance Directive
- Consent/withdrawal of consent for contact regarding future studies related or unrelated to PPMI
- Review willingness to share contact information with FOUND or, if enrolled in FOUND, review individual status report
- PPMI Brain and Tissue Bank (for subjects who did not yet sign a form providing permission to be contacted by the Brain and Tissue Bank study team or have not yet signed an Intent to Donate form, review subject interest in PPMI Brain and Tissue Bank and remind interested subjects to follow up with the Brain and Tissue Bank study team or have subject sign an Intent to Donate form)
- General neurological examination
- Vital signs
- Blood draw for research samples
- Blood draw for PBMCs
- PASE Exercise Questionnaire
- Epworth Sleepiness Scale
- REM Sleep Behavior Disorder Questionnaire
- GDS-15
- State-Trait Anxiety Inventory for Adults
- Questionnaire for Impulsive-Compulsive Disorders
- SCOPA-AUT
- Montreal Cognitive Assessment (MoCA)
- Letter Number Sequencing
- Hopkins Verbal Learning Test – Revised (use next subsequent form; see PPMI Operations manual for schedule of forms)
- Symbol Digit Modalities Test (alternate form 1 and 2; see PPMI Operations manual for schedule of forms)
- Benton Judgment of Line Orientation (alternate odd and even items; see PPMI Operations manual for schedule )
- Semantic Fluency (animals only)
- Cognitive Categorization Assessment
- Trails A and B
- Lexical Fluency (FAS)
- Boston Naming Test

- Determination of Falls
- NeuroQOL
- UPSIT
- MDS-UPDRS Parts I-III (Part IV also conducted at each visit for subjects who have started PD medication)
- Hoehn and Yahr
- Modified Schwab & England
- MDS-UPDRS Part III and Hoehn & Yahr will be repeated one hour following dosing in clinic for subjects who have started levodopa or dopamine agonist
- Participant Questionnaire
- DAT imaging
- Lumbar puncture for collection of CSF
- Review of current medical conditions
- Review of concomitant medications
- Review of adverse events related to lumbar puncture or DAT imaging (if lumbar puncture or DAT imaging performed)

#### **5.3.28 Study visits for Genetic Registry**

Once sites receive amendment 13 approval, all visits will cease for Genetic Registry subjects. Genetic Registry subjects who are enrolled in FOUND in PPMI will have the opportunity to continue to be followed through FOUND in PPMI. Genetic Registry subjects will complete one final phone visit following site's approval of amendment 13. (At the site's discretion, the final Genetic Registry visit may be done in person if deemed appropriate.)

This final phone visit will include the following activities:

- Verbal consent
- Review of clinical diagnosis
- Review of current medical conditions
- Review willingness to share contact information with FOUND or, if enrolled in FOUND, review individual status report.
- Review subject status regarding enrollment in PPMI Brain and Tissue Bank

## **6. Study Assessments**

### **6.1. Clinical Assessments**

#### **6.1.1. MDS-UPDRS**

The MDS-UPDRS is a multimodal scale assessing both impairment and disability and is separated into 4 subscales (Parts I-IV). The MDS-UPDRS includes components assessed by the study investigator as well as sections completed by the subject. Every effort should be made to have the same investigator perform the ratings for an individual subject throughout the course of the study.

- Part I: This assesses non-motor experiences of daily living and is comprised of two components:
  - ❖ Part IA contains 6 questions that are assessed by the Investigator and focuses on complex behaviors.
  - ❖ Part IB contains 7 questions that are part of the Patient Questionnaire completed by the subject.
- Part II: This assesses motor experiences of daily living. There are an additional 13 questions that are also part of the Patient Questionnaire completed by the subject.
- Part III: This assesses the motor signs of PD and is administered by the Investigator.
- Part IV: This assesses motor complications, dyskinesias and motor fluctuations using historical and objective information. The Investigator will complete this assessment at each visit once a subject has started PD medication.

Subjects (except Registry-PD subjects) who have started PD medication (levodopa or dopamine agonist) will have an annual assessment of the motor exam (Part III) and Hoehn and Yahr in a practically defined off state and then these assessments will be repeated one hour after receiving medication in clinic. These subjects will need to be reminded not to take PD medication on the day of each annual study visit. If possible, subjects on PD medication who withdraw prematurely from the study should also have the Part III assessment one hour after receiving medication during the Premature Withdrawal Visit.

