| Statistical Methods | Changes from baseline to the one year, two year, three year, four year and five years evaluations will be calculated and summarized descriptively. We will calculate 95% confidence intervals for the mean rate of change and between subject variability, For this purpose the between subject variability will be estimated by fitting mixed models to all available data. Correlations will be calculated between the different measures, for example between change in total MDS-UPDRS and change in DAT uptake or alpha-synuclein levels.                                                                                                                                                                                                                                                                                                                                                                                                                                                                                                                                                                                                                                                                                                                                                                                                                                                                                                                                                                                                                                                                                                                                 |

|                    |                                                                                                                                                                                                                                                                                                                                                                                               |
|--------------------|-----------------------------------------------------------------------------------------------------------------------------------------------------------------------------------------------------------------------------------------------------------------------------------------------------------------------------------------------------------------------------------------------|

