### **3. Study Outcomes**

#### **3.1 Primary Outcomes**

The mean rates of change and the variability around the mean of clinical, imaging and biomic outcomes in early PD patients, and where appropriate the comparison of these rates between PD patient subsets and between various subsets (including, but not limited to: PD vs. healthy subjects, PD vs. SWEDD, PD vs. prodromal, PD with and without LRRK2, GBA or SNCA mutation, unaffected LRRK2, GBA or SNCA mutation carriers vs. healthy subjects) at study intervals ranging from 3 months to 36 months. Specific examples of outcomes include MDS-UPDRS, dopamine transporter striatal uptake, vesicular monoamine transporter type-2 uptake, and serum and CSF alpha-synuclein. PD patient subsets may be defined by baseline assessments, genetic mutation, progression milestones and/or rate of clinical, imaging, or biomic change.

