**5.3.9. Visit 05 (18 months  $\pm$ 30 days)**

- Review of continuing ability to consent/Advance Directive
- Review willingness to share contact information with FOUND or, if enrolled in FOUND, review individual status report
- PPMI Brain and Tissue Bank (if subject has not yet been approached regarding Brain and Tissue Bank, review subject interest in sharing contact information with PPMI Brain and Tissue Bank study team or discuss Brain and Tissue Bank and present Intent to Donate form to subject)
- Vital signs (blood pressure, heart rate and temperature)
- Blood draws for research samples (including blood draw for PBMCs)
- MDS-UPDRS Parts I-III (PD, Prodromal SWEDD, and Genetic Cohort subjects only) (Part IV also conducted for subjects who have started PD medication)
- Hoehn and Yahr scale (PD, Prodromal, SWEDD and Genetic Cohort subjects only)
- Modified Schwab & England (PD, Prodromal, SWEDD and Genetic Cohort subjects only)
- Clinical diagnosis assessment (Prodromal, SWEDD and Genetic Cohort subjects only)
- Review of family history of PD (Genetic Cohort subjects only)
- Review of current medical conditions
- Review of concomitant medications
- Consent/withdrawal of consent for contact regarding future studies related or unrelated to PPMI

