## 7. Concomitant Medications

### 7.1.1. Initiation of PD Medications

It is anticipated that the majority of PD (and SWEDD) subjects will be able to remain off PD medications for at least 6 months after Baseline. However, PD medications may be initiated at any time after enrollment at the discretion of the patient or treating physician (inclusive of Prodromal and Genetic Cohort PD subjects). The medication used is at the discretion of the treating physician. It is anticipated that the majority of Genetic Cohort-PD and Registry-PD subjects may be on PD medications at baseline. If PD medications are to be initiated, subjects (except the Genetic Registry) will be asked to return for an ST

visit. The investigator will document any new medications or changes in medication at each study visit on the Concomitant Medication Log.

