The table below provides generic information about the detectable effect sizes for three types of statistical analysis that may be performed on the PPMI data. For each analysis the two-sided alpha level is set to 0.05 and the beta level to 0.80. The first column gives the total sample size assumed to be available for the analysis, in the first two rows either 400 (total PD sample) or 300 (PD sample after allowance for 25% withdrawals). The third and fourth rows of the table correspond to the total sample size of 600 (400 PD, 200 HC) when, respectively 75% and 100% of the subjects are available for analysis. The second column gives the detectable correlation coefficient between two continuous measures (e.g., change in striatal  $\beta$ -CIT uptake vs. change in total MDS-UPDRS). The third column gives the detectable difference in prevalence rates of some characteristic (e.g. presence of dopaminergic side effects) between two “halves” of the sample (e.g. the younger patients vs. the older patients, with age dichotomized at the median for the entire group). For the first two rows the third column gives the detectable “effect size”, expressed as ratio of difference in means to standard deviation, for comparing two “halves” of the sample (e.g. younger vs. older patients as above) in relation to a continuous measure (e.g. change in total MDS-UPDRS). For the third and fourth row the comparisons are between PD patients and HC. The table suggests that the PPMI trial is adequately powered to detect effects that would generally be of clinical interest. While possible that smaller effects than those listed in the table might also be of clinical interest, it was determined that the added power for these comparisons did not offset any additional costs and logistical issues that would accompany a larger study in this population. Rather, the proposed study should prove to be effective for screening a large number of variables and identifying those that show the most promise for further exploration in follow-up studies.

| Total sample size | Detectable Correlation | Detectable Difference in Prevalence | Detectable Difference in Means (Standardized) |
|--------------------------|-------------------------------|--------------------------------------------|------------------------------------------------------|

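### Treated subjects' motor ratings are fixed as OFF only at annual visits, yet the variance models take all available data; applied as written to MDS-UPDRS, this mixes medication states

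*Protocol*

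**What the plan says.** **Medication state.** Section 6.1.1 states that subjects who have started levodopa or a dopamine agonist "will have an annual assessment of the motor exam (Part III) and Hoehn and Yahr in a practically defined off state", repeated one hour after dosing in clinic. The instruction to withhold is limited to the same visits: "These subjects will need to be reminded not to take PD medication on the day of each annual study visit".

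**Interim ratings.** PD subjects are also rated at Months 3, 6, 9, 18, 30, 42 and 54 (Sections 5.3.5 to 5.3.15). Section 5.3.9 (Month 18) is typical: "MDS-UPDRS Parts I-III (PD, Prodromal SWEDD, and Genetic Cohort subjects only) (Part IV also conducted for subjects who have started PD medication"). None of these sections names a medication state.

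**Start of treatment.** Section 7.1.1: "PD medications may be initiated at any time after enrollment at the discretion of the patient or treating physician". The same section expects most PD subjects to stay untreated for at least six months.

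**Outcome and analysis.** Section 3.1 defines the primary outcome as mean rates of change and their variability "at study intervals ranging from 3 months to 36 months. Specific examples of outcomes include MDS-UPDRS", among others. The Synopsis (Statistical Methods) describes changes from baseline at years one to five. It then announces 95% confidence intervals for the mean rate and the between-subject variability, for which "the between subject variability will be estimated by fitting mixed models to all available data". Section 14.4 leaves further detail to a Data Analysis Plan that is not at hand.

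**The concern.** The visit scheme yields two kinds of Part III score in treated subjects: OFF at annual visits, and undefined, possibly ON, in between. A model that takes every visit treats both as one measure. Ratings lowered by medication sit mostly in the later half of the 36 months, so they pull the fitted slope down, and the alternation between states appears as residual noise. Section 1.1 itself warns that symptomatic drugs can confound clinical outcomes.

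The study exists to supply rates and variances for use in trials of disease-modifying therapies, so an error here passes into other studies. It would also fall unevenly across cohorts. Healthy controls have MDS-UPDRS only at baseline and annual visits, so state mixing enters only the PD side of a PD versus control comparison of rates.

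**Working it through.** **1. The plan's own figure.** Section 14.5 gives no MDS-UPDRS rate or SD, only generic detectable effects: "For each analysis the two-sided alpha level is set to 0.05 and the beta level to 0.80" (0.80 is read as power), with "either 400 (total PD sample) or 300 (PD sample after allowance for 25% withdrawals"). For two halves of 400, d = (1.960 + 0.842) × √(1/200 + 1/200) = 0.280, against 0.28 stated. The figure reproduces, but it is in SD units and cannot size the present problem.

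**2. Slope bias for one treated subject.** Idiopathic PD visits to Month 36 are 0, 3, 6, 9, 12, 18, 24, 30 and 36. Their mean is 138/9 = 15.33 months, and Sxx = 3366 − 138²/9 = 1250 months² = 8.68 years². If interim visits after treatment starts are ON by g points and annual visits are OFF, least squares gives

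bias = −g × Σ(t − mean, over ON visits) / Sxx.

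- Start just after Month 6 (ON at 9, 18, 30): −(11.00/12)/8.68 = −0.106 points/year per point of gap
- Start just after Month 12 (ON at 18, 30): −(17.33/12)/8.68 = −0.166
- Start just after Month 24 (ON at 30): −(14.67/12)/8.68 = −0.141

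At an assumed 6-point gap this is about −0.6 to −1.0 points/year.

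**3. Symptomatic Therapy (ST) visits.** Under Section 5.3.24 an untreated ST visit can replace the next visit. If it fills the Month 18 slot, only Month 30 is ON: −0.141 instead of −0.166. If it fills the Month 9 slot, ON visits are 18 and 30: −0.166 instead of −0.106. ST visits change the bias but do not remove it.

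**4. Whole cohort.** None of the following inputs is in the protocol; all are assumed. True slope 3 points/year, slope SD 2, residual SD 4. Gap 3, 6 or 10 points, with between-subject SD half the gap. Treatment begun in 15% during Months 0 to 6, reaching 50% or 80% by Month 24. Half or all treated interim ratings ON. ST visits are not modelled. With 100,000 simulated subjects, each subject's least-squares slope was taken, residual variance pooled, and slope variance computed as Var(fitted slopes) − residual variance/Sxx. On complete balanced data this equals the REML random-slope fit.

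| Gap | Treated | Interim ON | Slope | Residual SD | Slope SD |
|---|---|---|---|---|---|
| 0 | 80% | all | 2.99 | 4.00 | 2.00 |
| 3 | 50% | half | 2.94 (−2%) | 4.09 (+2%) | 1.99 (−0.5%) |
| 6 | 50% | all | 2.73 (−9%) | 4.57 (+14%) | 1.93 (−3.5%) |
| 6 | 80% | all | 2.46 (−18%) | 4.81 (+20%) | 1.88 (−6%) |
| 10 | 80% | all | 2.10 (−30%) | 6.00 (+50%) | 1.66 (−17%) |

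**5. A limit of these figures.** They apply to the idiopathic PD grid. A Genetic Cohort PD subject already treated at baseline, and assumed to be rated OFF there, is seen at 0, 6, 12, 18, 24, 30 and 36. ON visits at 6, 18 and 30 lie −12, 0 and +12 months from the mean of 18, so the slope bias is zero and only residual variance rises.

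**The case against.** The strongest reply is that choosing a Part III score or a medication covariate belongs in the Data Analysis Plan. That would hold if the protocol were silent. It is not: it states a data rule, and that rule applied to its own visit scheme mixes states. A later plan may repair this, but the protocol text does not.

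Other parts of the reply stand and limit the point.

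- The descriptive changes at years one to five use annual visits. PD subjects enter untreated (Section 4.2.2), so with the OFF score these changes are state-consistent. A reader might infer that every MDS-UPDRS rate is distorted; the text does not support that.
- The Synopsis sentence names between-subject variability. It does not say that the mean rate is a slope through every rating.
- A reader might infer that one-hour post-dose repeats are pooled too. They are a separate schedule item, and nothing puts them in a rate model.
- The mixed model in Section 14.4.2 covers the first six months, when most PD subjects should be untreated.
- Interim ratings being ON is an assumption. Without a withholding instruction it is plausible, but the protocol does not say so.
- A reader might infer that mean change at Month 18 takes the wrong sign. On the step 4 assumptions with 80% treated, true change is 1.5 × 3 = 4.5 points and the share treated by Month 18 is 0.15 + 0.65 × 12/18 = 0.58. With all interim ratings ON, a 6-point gap leaves 4.5 − 3.5 = +1.0. Only the 10-point gap turns it negative (4.5 − 5.8 = −1.3).
- The issue concerns Part III, Hoehn and Yahr and totals built on Part III. MDS-UPDRS is one of several example outcomes, and after Month 60 the modified schedule has only annual in-person ratings.

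**Conclusion.** The point holds in conditional form. OFF rating is fixed only for annual visits, interim visits within the primary window leave the state open, and the stated rule sends all of them into the models for variability and for the confidence intervals around the mean rate. If interim ratings in treated subjects are wholly or partly ON, a slope pooled over the idiopathic PD visits is too low and residual variance too high.

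Variance is not simply inflated: between-subject slope SD, the quantity closest to what the Synopsis names, moved down in these calculations while residual SD moved up. The range of −2% to −30% for the slope rests wholly on the assumed gap, treated share, share rated ON, true slope and SDs; at its low end the effect is trivial. The direction follows from the visit grid and the ON assumption. This is worth correcting before any MDS-UPDRS rate or variance is modelled, because the change is small and the estimates are meant for reuse.

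**What to change.** In the Synopsis (Statistical Methods) and Section 14, replace the all-available-data rule for Part III, total MDS-UPDRS and Hoehn and Yahr with this: all visits before PD medication starts, including ST visits, plus annual OFF assessments afterwards. State that one-hour post-dose repeats do not enter the rate or variance models. Since the OFF rule names only levodopa and dopamine agonist users, also say which annual score is used for subjects on other PD drugs alone.

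Analyse interim post-medication scores only in a sensitivity model with a time-varying term for being on PD medication and visit type (annual OFF or interim). Both are already recorded. Time since last dose is not required by the protocol text, so this term stands in for the true state at interim visits.

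The cost is fewer usable Part III ratings after treatment starts, and so some loss of precision. No visit is added, and no treatment or dosing rule changes.

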#### **6.1.2. Hoehn and Yahr Stage**

The Hoehn and Yahr is a commonly used system for describing how the symptoms of Parkinson disease progress. The scale allocates stages from 0 to 5 to indicate the relative level of disability. This scale is included within the MDS-UPDRS and will be completed for all subjects.

- Stage zero: No symptoms.
- Stage one: Symptoms on one side of the body only.
- Stage two: Symptoms on both sides of the body. No impairment of balance.
- Stage three: Balance impairment. Mild to moderate disease. Physically independent.
- Stage four: Severe disability, but still able to walk or stand unassisted.
- Stage five: Wheelchair-bound or bedridden unless assisted.

#### **6.1.3. Modified Schwab & England Activities of Daily Living**

The Modified Schwab & England Activities of Daily Living (ADL) scale reflects the speed, ease, and independence with which an individual performs daily activities, or personal chores, such as eating, toileting, and dressing. This scale uses a rating scale from 0% to 100%, with 100% representing complete independence in performing daily activities and 0% representing a vegetative, bedridden state.

